### 2.4. Recruitment and Randomisation 

#### 2.4.1. Sample Size

The sample size calculation and power of the study are based on the data of previously reported studies contrasted, combined, and synthesised in our recent systematic review and meta-analysis [1]. We considered following the formula $n=\;\frac{2{\left(Z_{\alpha }\;+\;Z_{1-\beta }\right)}^{2}\sigma^{2}}{\Delta^{2}}$, where *n* is the required sample size, *Z_α_* and *Z*_(1 − *β*)_ are the constants set by convention according to the accepted *α* error and power of the study, respectively, *σ* is the estimated standard deviation, and Δ is the expected effect size. Therefore, we expect to detect an effect size of −8.36 on AHI (pooled raw mean difference of previous trials) [1], considering a type 1 error/α error of 5% (*Z_α_* = 1.64), and a statistical power of 90% (*Z*_(1 − *β)*_ = 1.28). Regarding the estimated AHI variability, we established an *σ* of 11.98, considering the AHI pooled standard deviation of all independent samples included in our previous research [1]. As a result, the expected sample size is ≈35 participants per arm of our controlled clinical trial. However, assuming a maximum of a 17.25% drop-out rate (based on the average drop-out rate of previous studies [1]), we decided to recruit a total sample size of ≈42 participants for each study group. Thus, a total of ≈84 patients with moderate to severe OSA will be enrolled in the INTERAPNEA study. For practical and feasibility reasons, and based on our previous experience [25,26], the study will be conducted in sets of a maximum of 30 persons.

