### 2.5. Assessment/Outcome Variables

The primary outcome of the INTERAPNEA study is the reduction in the number of apnoea and/or hypopnoea episodes per hour, i.e., AHI, assessed using a full-night ambulatory polysomnography. The main secondary outcomes include other neurophysical and cardiorespiratory polysomnographic outcomes, body weight and composition, physical fitness/cardiorespiratory fitness, and health blood biomarkers. Other variables of interest are subjective measurements of depressive and anxiety symptomatology related to OSA, impaired sleep (i.e., daytime sleepiness, sleep quality, and functional outcomes of OSA), health-related quality of life, and other lifestyle habit measurements (i.e., diet, physical activity, alcohol and tobacco consumption). All outcomes will be measured at baseline (week 0), intervention end-point (week 9), and 6 months post-intervention (week 32).

Assessment of primary and secondary outcomes will be organised and completed over three different days during a one to two-week period:Day 1: Potential participants will attend a medical examination and a fasting blood test at the Sleep Unit of “Virgen de las Nieves” University Hospital.Day 2: Eligible participants will complete a full-night in-laboratory polysomnography (PSG; the gold-standard objective testing recommended by the AASM [29]), at the Sleep and Health Promotion Laboratory (CIMCYC). In order to avoid potential CPAP influence on PSG outcomes, participants will be required to withdraw from CPAP during the week prior to the PSG at baseline and follow-ups [30]. Prior to PSG, participants will also complete a set of questionnaires measuring subjective variables related to sleep, general physical and psychological health, and lifestyle habits including diet, physical exercise, and alcohol and tobacco consumption.Day 3: During the third and last assessment day, participants will be required to attend the iMUDS for the measurement of anthropometric parameters, body composition and cardiorespiratory fitness.

Baseline physical activity and sleep habits will also be obtained through a seven-day self-reported daily step log and sleep diary. See Table 2 for study outcomes and measurements.

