### 2.9. Analytical Approach and Statistical Power/Data Management

We will perform descriptive and exploratory preliminary analyses of all the study variables to reveal violations of statistical assumptions, distributions, imbalances between the study groups, associations between study variables, covariates/confounders, amount of missing data, and drop-out patterns. Covariates or confounders will be secondarily included in the main statistical analysis, evaluating therefore, their impact on the results. To ensure that conclusions are robust, attrition bias will be overcome through intention-to-treat-analysis (ITT), including all participants as originally allocated after randomisation using multiple imputation methods for predicting end-points missing values. Per-protocol comparison of groups, including only those participants who fully completed the originally allocated treatment, will also be computed and compared with ITT analysis results.

The intervention effects on primary and secondary study outcomes will be assessed through multi-level mixed analyses using the package *nlme* [96] from the R statistical program. This method will allow us to analyse differences including time and group allocation as within and between subject factors, respectively, adjusting for potential covariates and levels such as group or set of participants. Therefore, group/condition will be considered as a fixed variable (intervention group compared to control group), and sets/waves of participants as a random factor. With these specifications, we will be able to control the intra-class correlation (per set of participants nested within conditions) between scores at baseline and post-test or follow-up. We will adjust the model including the baseline values of outcomes that are to be analysed in the specific analysis as covariates, as well as other potential covariates such as age, OSA severity, BMI, motivation to change, and attrition propensity. The latter will be calculated using a model predicting the actual attrition with baseline values [97]. Baseline measurements included in these attrition propensity prediction models will include set of participants, participant’s allocation, age, OSA severity, BMI, and motivation to change. The primary and secondary study outcomes that are to be analysed will be those previously mentioned in the outcomes section.

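### As worded, the mixed model appears to use the baseline value both as a response row and as a covariate, and it does not say which treatment contrast is reported

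*Protocol article*

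**What the plan says.** Section 2.5 gives three measurement times: "All outcomes will be measured at baseline (week 0), intervention end-point (week 9), and 6 months post-intervention (week 32"). Section 2.9 describes one multi-level mixed model for the primary and all secondary outcomes and makes four statements about it that matter here:

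- The model compares participants "including time and group allocation as within and between subject factors, respectively".
- Group is a fixed effect, intervention against control, and the set (wave) of participants is a random factor. No group-by-time term is named.
- These specifications are said to control the intra-class correlation, by set within condition, "between scores at baseline and post-test or follow-up".
- On covariates, the section says: "We will adjust the model including the baseline values of outcomes that are to be analysed in the specific analysis as covariates", together with age, OSA severity, BMI and other covariates.

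Earlier in the same section, covariates are said to enter the main analysis secondarily. The section ends with a standardised effect size built on the between-arm difference in mean change from baseline to post-intervention.

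**The concern.** A correlation between baseline and later scores is something a model can account for only if baseline scores are among the responses. Adjusting for the baseline value as a covariate is the usual partner of a model whose responses are all post-baseline. Section 2.9 asks for both, and no sentence takes week 0 out of the response. The week-0 response would then be explained by itself.

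What follows depends on which coefficient is reported, and the section does not say. A group main effect would average in a time point before treatment began. A group-by-time contrast would leave the baseline covariate idle. Two analysts following the text faithfully could report different treatment effects for AHI from the same data.

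**Working it through.** **Inputs from the documents (section 2.4.1).** The planned effect is given as "we expect to detect an effect size of −8.36 on AHI". The standard deviation is stated as "of 11.98, considering the AHI pooled standard deviation of all independent samples included in our previous research". Z values are 1.64 (α of 5%) and 1.28 (power of 90%), with about 35 per arm before drop-out.

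**Assumptions.** The baseline-to-follow-up correlation ρ is not given, so a range of 0.3 to 0.8 is shown. The variance is taken as equal at all times, and the correlation as equal between any two times.

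**The plan's own figure.** n = 2(1.64 + 1.28)² × 11.98² / 8.36² = 35.02 per arm. The stated 35 reproduces. Allowing for drop-out, 35/(1 − 0.1725) = 42.3, consistent with the stated 42.

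**Reading A: group main effect, with rows at weeks 0, 9 and 32 and baseline as covariate.** Given the baseline value, the arms cannot differ at week 0, so that row contributes exactly 0. For a constant effect d:

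- group coefficient = (0 + d + d)/3 = 2d/3
- with d = −8.36: 2 × (−8.36)/3 = −5.57

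A simulation of 120 trials per setting, with 35 per arm and a participant random intercept, gave −5.55 at ρ = 0.5 and −5.57 at ρ = 0.7. Baseline-adjusted analysis of the average of weeks 9 and 32 gave −8.32 and −8.35. The model standard error fell in the same proportion. At ρ = 0.5 it was 1.35 against 2.03, and 2.03 × 2/3 = 1.35. Simulated power was 0.967 for both analyses.

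The factor of two thirds is specific to three rows and a constant effect. If the effect were present only at week 9, the coefficient would be (0 + d + 0)/3, one third of the week-9 effect.

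**Reading B: group-by-time contrast at week 9, same rows.** The baseline covariate is constant within a participant, so it cannot alter a within-participant contrast. In the simulation, the estimate and standard error were the same with and without it (ρ = 0.5: −8.38, SE 2.82; ρ = 0.7: −8.24, SE 2.22). What remains is a comparison of change scores:

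- change score: SE = 11.98 × √[2(1 − ρ) × 2/35]
- baseline-adjusted: SE = 11.98 × √[(1 − ρ²) × 2/35]
- variance ratio = 2(1 − ρ)/(1 − ρ²) = 2/(1 + ρ)
- power = Φ(8.36/SE − z), with z = 1.96 (two-sided 5%) or z = 1.64 (the protocol's constant)

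| ρ (assumed) | SE change | SE adjusted | Variance ratio | Power, z = 1.96: change / adjusted | Power, z = 1.64: change / adjusted |
|---|---|---|---|---|---|
| 0.3 | 3.39 | 2.73 | 1.54 | 69% / 86% | 80% / 92% |
| 0.5 | 2.86 | 2.48 | 1.33 | 83% / 92% | 90% / 96% |
| 0.7 | 2.22 | 2.05 | 1.18 | 96.5% / 98.3% | 98.3% / 99.3% |
| 0.8 | 1.81 | 1.72 | 1.11 | 99.6% / 99.8% | 99.9% / 99.9% |

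At ρ = 0.5 the change score has the same variance as the raw score, since 2(1 − 0.5) = 1. Reading B then delivers just the planned 90% with the protocol's own constant.

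**The case against.** **Time may mean weeks 9 and 32 only.** No sentence lists the response rows. With two follow-ups, time is still a within-subject factor, and baseline as covariate then fits naturally. The clause on correlation carries a parenthesis about sets within conditions, so it is partly about clustering. This reading is possible and would remove the problem. It fits poorly with a clause that names baseline scores as one side of the correlation, so the text is at best ambiguous.

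**Covariates enter secondarily.** The first model may therefore have no baseline covariate. The later sentence on baseline adjustment carries no such condition, and the adjusted model would still have the double use.

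**The effect size points to a change contrast.** The formula at the end of section 2.9 is a difference in mean change, which is not diluted. This stands. A reader might infer that the trial will report an effect one third too small. The documents do not support that as a prediction, because it needs the group main effect to be the reported term, and a condensed article may leave an interaction term to a fuller document.

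**Power.** A reader might also infer that the trial is underpowered for this reason. Under Reading A with a participant effect, the test loses nothing. Under Reading B, the sample size was set on the raw standard deviation with no credit for baseline adjustment, so the loss is of efficiency that the calculation never counted on. The 83% at ρ = 0.5 falls below 90% only because it is two-sided while the protocol's constant is 1.64, which is a separate matter.

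**Conclusion.** The point holds as a defect of specification in the primary analysis. The natural reading of section 2.9 uses baseline twice, and the contrast is not fixed.

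- If the group main effect is reported, the AHI effect is understated by one third (−5.57 for a true −8.36 at both follow-ups). The test is unharmed provided a participant random effect is fitted.
- If group-by-time is reported, the estimate is unbiased and the test valid, but the baseline covariate is inert. The variance is higher by 54%, 33%, 18% and 11% at ρ of 0.3, 0.5, 0.7 and 0.8. The power cost is material at low to moderate ρ and small from 0.7 upwards.

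The two-thirds factor rests on three response rows and a constant effect, and the efficiency figures rest on an assumed ρ. Severity is moderate: the wording should be settled before analysis, but neither reading invalidates the trial.

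**What to change.** In section 2.9, state the response rows and the contrast. Use only weeks 9 and 32 as responses. Fixed effects are arm, time, arm by time and the baseline value of the outcome; participant is the repeated-measures unit; set stays as the planned random factor. Report the arm difference at week 9, the intervention end-point, from this model.

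An equally valid alternative is to keep week 0 as a response row with a common baseline mean across arms, and to drop the baseline covariate.

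Either change is a rewording of the model in about two sentences. It needs no new data, no change in sample size and no change in trial conduct.

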## 3. Potential Impact of INTERAPNEA

OSA is a global health issue with a concerning and increasing prevalence associated with the rising epidemic of obesity [9,13]. Both these related conditions are predisposing factors for the development and worsening of metabolic dysfunctions, type II diabetes, and, in turn, life-threating cardiovascular diseases such as heart failure, atrial fibrillation, coronary artery disease and stroke [99]. Due to these vast and severe health consequences, besides the direct cost of OSA diagnosis, treatment, and workplace and motor vehicle accidents produced by daytime sleepiness, OSA has become a substantial clinical and economic burden on the health system [100].

An epidemiological study by Hillman et al. [101], concluded that the overall cost of sleep disorders in Australia—with OSA as the most prevalent condition—was $7494 million in 2004 (population: 20.1 million), including direct health costs (i.e., sleep disorders and associated conditions), indirect financial costs (i.e., work-related injuries, motor vehicle accidents, and other production losses), and nonfinancial costs (net cost of suffering). Taking into account that the prevalence of OSA has dramatically increased in recent years (9% to 38% in the overall population) [9], the cost should respectively now be ominously higher. Other retrospective and longitudinal studies have also emphasised the major clinical and financial costs of OSA by reporting significantly greater healthcare utilisation by patients with this condition compared to those without OSA [102,103,104,105]. Furthermore, a recent study by Derose et al. [106] concluded that even after the provision of positive airway pressure, the rates of acute care and medication use of patients with OSA did not reduce over several years of follow-up.

The INTERAPNEA study is aimed at demonstrating the potential and beneficial effects of a non-pharmacological and non-surgical tailored weight loss and lifestyle intervention for the management, improvement, and even complete remission of OSA. Although a number of studies have separately shown that physical exercise and diet may improve OSA primary outcomes, there is a lack of studies including a combination of both weight loss components [1]. Furthermore, there are no studies including active intervention components addressing tobacco and/or alcohol avoidance in patients with this condition [1] despite the well-evidenced severe consequences that smoking and alcohol intake have on OSA and comorbid diseases [20,21,89,93,94].

To our knowledge, this is the first study to describe the effects of a well-established interdisciplinary weight loss and lifestyle intervention on the primary and secondary outcomes of OSA, and other important physical and psychological health-related outcomes such as blood biomarkers, body composition, cardiovascular risk, daytime functioning and mood, and general quality of life. The inclusion of all these secondary outcomes, in turn, will potentially allow us to determine which may be the key variables mediating and/or predicting the main changes in OSA. The use of objective measurements ensuring validity of results such as full-night PSG, blood test, body composition, and cardiorespiratory fitness, besides the addition of psychological/coaching support on the design and implementation of the intervention components, provides the INTERAPNEA study with unique and strong characteristics in this field of research.

In conclusion, the INTERAPNEA study will overcome all the shortcomings found in previous OSA research and, therefore, our findings will have a potential impact not only on the knowledge and management of this condition but also on high-risk comorbidities such as obesity, type II diabetes, cardiovascular disease, and neurocognitive dysfunctions. Considering the feasibility of the intervention in real life settings, it may contribute to the standardisation of a cost-effective treatment for preventing, improving and/or curing the severe health-consequences of this increasingly common sleep-disordered breathing.

## Figures and Tables

**Figure 1 nutrients-11-02227-f001:**
[figure not shown]
Flow diagram of the INTERAPNEA study participants.

**Table 1 nutrients-11-02227-t001:** Eligibility criteria.

Inclusion Criteria	Exclusion Criteria
Men aged 18–65 years CPAP-treated moderate to severe OSA (AHI equal to or greater than 15 events/h) BMI equal to or greater than 25 kg/m^2^ Not participating in a weight loss program Willing to provide informed consent and acceptance of random group assignment	Presence of any other primary sleep disorder Presence of any mental disorder (including depression, anxiety, and addiction to alcohol or other substances) Presence of any other severe organic disease, except for those comorbid to OSA Regular use of neuroleptic, sedative or hypnotic drugs, or any other medication that may cause sleep disturbances or increased daytime sleepiness

AHI = apnoea-hypopnoea index; BMI = body mass index; CPAP = continuous positive airway pressure; OSA = obstructive sleep apnoea.

**Table 2 nutrients-11-02227-t002:** INTERAPNEA study outcomes and measurements.

Variable	Measurement	Assessment
General health history and sociodemographic information	General medical examination (i.e., anamnesis, physical exploration, vital measurements, etc.)	Week 0
	Clinical and socio-demographic interview	Week 0
	Fasting blood test	Week 0, 9, 32
Sleep quality and health-related quality of life		
Sleep habits	Sleep diary	Week 0, 9, 32
Circadian preference/chronotype	Morningness-Eveningness Questionnaire	Week 0, 9, 32
Sleep quality	The Pittsburgh Sleep Quality Index	Week 0, 9, 32
Daytime sleepiness	Epworth Sleepiness Scale	Week 0, 9, 32
	Psychomotor Vigilance Test	Week 0, 9, 32
Perceived health-related quality of life	Sleep Apnea Quality of Life	Week 0, 9, 32
	Short-Form 36 Health Survey	Week 0, 9, 32
	General Health Questionnaire	Week 0, 9, 32
Objective sleep		
Neurophysiological outcomes	Polysomnography equipment	Week 0, 9, 32
Cardiorespiratory outcomes	Polysomnography equipment	Week 0, 9, 32
Body weight and composition		
BMI and anthropometric measurements	Weight and height measurement, and neck, chest and waist circumferences	Week 0, 9, 32
Body composition	Dual Energy X-ray Absorptiometry	Week 0, 9, 32
Lifestyle habits		
Physical exercise habits	Spring-levered pedometer and daily step logs	Week 0, 9, 32
Dietary habits	Food Behaviour Checklist	Week 0, 9, 32
	Mediterranean Diet Adherence Screener	Week 0, 9, 32
Tobacco dependence and consumption	Self-reported tobacco consumption logs	Week 0, 9, 32
	The Fagerstrom Test for Nicotine Dependence	Week 0, 9, 32
Alcohol consumption	Self-reported alcohol consumption logs	Week 0, 9, 32
Physical fitness		
Cardiorespiratory fitness	2 km walk test	Week 0, 9, 32
Subjective physical fitness	International Fitness Scale	Week 0, 9, 32
Daily functioning and mood		
Functional outcomes related to sleepiness	Functional Outcomes of Sleep Questionnaire	Week 0, 9, 32
Subthreshold anxiety symptoms	State-Trait Anxiety Inventory	Week 0, 9, 32
Subthreshold depression symptoms	Beck Depression Inventory-Fast Screen	Week 0, 9, 32
	Inventario de Depresión Estado-Rasgo	Week 0, 9, 32

**Table 3 nutrients-11-02227-t003:** Description and timing of the INTERAPNEA intervention modules and components.

Module	Objectives/Description	Number of Sessions	Frequency of Sessions	General Behavioural Change Techniques
Nutritional behaviour change	Nutrition education and dietary patterns change	8	Once a week	Motivation and preparation for action Goal-setting and action-planning Self-monitoring and functional behavioural analysis Review of behavioural goals, action plans, and adherence Problem solving and social skills Self-efficacy, maintenance, and relapse prevention
Physical exercise	Supervised moderate aerobic exercise and increase daily steps by 15% each week	8	Once a week	
Sleep hygiene	Change of inappropriate sleep habits: Insufficient sleep, consumption of coffee, alcohol and tobacco, and inappropriate sleep schedule and environment	4	Once every two weeks	
Tobacco cessation	Nicotine and cigarette fading: Reduction of nicotine and number of cigarettes by 30% each week	8	Once a week	
Alcohol avoidance	Alcohol consumption fading: Reduction of alcohol consumption by 30% each week	4	Once every two weeks	

**Table 4 nutrients-11-02227-t004:** Description of nutrition education per session.

Session	Nutrition Education Topics
Session 1	Adverse consequences of obesity, importance of healthy nutrition and body composition on health, and positive effects of changes in nutrition.
Session 2	Maintenance of a healthy nutrition based on the Harvard Plate model: increasing consumption of healthy food (vegetables, fruits, legumes, nuts, extra virgin olive oil, fish and shellfish, white meat, eggs and herbs) and decreasing consumption of unhealthy food (ultra-processed foods, excessive salt consumption, processed meats, red meat, alcohol, and high-calorie foods and beverages).
Session 3	Food myths and health risks of miracle diets.
Session 4	Strategies to improve satiety and decrease appetite: Decreasing dishes dietary energy density, choosing food with low dietary energy density, managing dietary fat intake, including enough fibre and protein, limiting sugar and ultra-processed foods, choosing water and low-calorie beverages, and managing portion sizes.
Session 5	Healthy breakfast and snacks: Avoiding unhealthy breakfasts and snacks and making them healthier.
Session 6	Healthy cooking, food purchase and choices when eating out.
Session 7	How to read nutritional labels of food and distinguish between healthy and unhealthy food.
Session 8	Nutritional strategies to improve sleep quality.

**Table 5 nutrients-11-02227-t005:** Summary of components of the sleep hygiene module per session.

Session	Intervention Objectives/Components
Session 1	Goal-setting and action-planning: Objective specification and commitment Self-monitoring: Sleep diary Psychoeducation: What is sleep hygiene? Cognitive restructuring: Irrational, false or inaccurate beliefs about sleep Breathing and relaxation techniques: Diaphragmatic breathing and progressive muscle relaxation
Session 2	Review of behavioural goals, action plans, and compliance (participant’s homework) Self-monitoring: Sleep diary Psychoeducation: Voluntary sleep restriction; coffee, alcohol and tobacco consumption before sleep; and irregular sleep schedule and environment Cognitive restructuring: Irrational, false or inaccurate beliefs about sleep Review of diaphragmatic breathing and progressive muscle relaxation
Session 3	Review of behavioural goals, action plans, and compliance (participant’s homework) Self-monitoring: Sleep diary Vicarious and self-reinforcement: Changes in sleep habits achieved and benefits Stimulus control and bedtime restriction Review of diaphragmatic breathing and progressive muscle relaxation
Session 4	Review of behavioural goals, action plans, and compliance (participant’s homework) Self-monitoring: Sleep diary Vicarious and self-reinforcement: Changes in sleep habits achieved and benefits Review of all intervention components: Main factors of sleep hygiene, diaphragmatic breathing and progressive muscle relaxation, stimulus control and bedtime restriction Maintenance and relapse prevention: Analysis of high risk situations for unhygienic sleep.

**Table 6 nutrients-11-02227-t006:** Summary of components of the smoking cessation module per session.

Session	Intervention Objectives/Components
Session 1	Goal-setting and action-planning: Objective specification and commitment Self-monitoring: Cigarette consumption logs Psychoeducation: Cigarette components and smoking consequences Cognitive restructuring: Irrational, false or inaccurate beliefs about smoking cessation Stimulus control: Reduction strategies Nicotine and cigarette fading: Reduction of nicotine/number of cigarettes by 30% from baseline Breathing and relaxation techniques: Diaphragmatic breathing and progressive muscle relaxation
Session 2	Review of behavioural goals, action plans, and compliance (participant’s homework) Self-monitoring: Cigarette consumption logs Cognitive restructuring: Irrational, false or inaccurate beliefs about smoking cessation Stimulus control: Smoking avoidance in three different situations and other reduction strategies Nicotine and cigarette fading: Reduction of nicotine/number of cigarettes by 30% from week 1 Maintenance and relapse prevention: Avoidance of withdrawal symptoms Review of diaphragmatic breathing and progressive muscle relaxation
Session 3	Review of behavioural goals, action plans, and compliance (participant’s homework) Self-monitoring: Cigarette consumption logs Vicarious and self-reinforcement: Changes in smoking achieved and benefits Stimulus control: Smoking avoidance in six different situations and other reduction strategies Nicotine and cigarette fading: Reduction of nicotine/number of cigarettes by 30% from week 2 Maintenance and relapse prevention: Avoidance of withdrawal symptoms Review of diaphragmatic breathing and progressive muscle relaxation
Session 4	Review of behavioural goals, action plans, and compliance (participant’s homework) Self-monitoring: Cigarette consumption logs Vicarious and self-reinforcement: Changes in smoking achieved and benefits Stimulus control: Smoking avoidance in nine different situations and other reduction strategies Nicotine and cigarette fading: Reduction of nicotine/number of cigarettes by 30% from week 3 Maintenance and relapse prevention: Avoidance of withdrawal symptoms Review of diaphragmatic breathing and progressive muscle relaxation
Session 5	Review of behavioural goals, action plans, and compliance (participant’s homework) Self-monitoring: Cigarette consumption logs Vicarious and self-reinforcement: Changes in smoking achieved and benefits Abstinence planning: Setting the day when abstinence starts Problem solving and social skills: High risk situations for smoking and alternative behaviours Maintenance and relapse prevention: Avoidance of withdrawal symptoms Review of diaphragmatic breathing and progressive muscle relaxation
Sessions 6, 7, 8	Review of behavioural goals, action plans, and compliance (participant’s homework) Self-monitoring: Cigarette consumption logs/review of abstinence Abstinence planning: Setting the day when abstinence starts Vicarious and self-reinforcement: Changes in smoking achieved and benefits Problem solving and social skills: High risk situations for smoking and alternative behaviours Review of diaphragmatic breathing and progressive muscle relaxation Maintenance and relapse prevention: Difference between lapse and relapse

**Table 7 nutrients-11-02227-t007:** Summary of components of the alcohol avoidance module per session.

Session	Intervention Objectives/Components
Session 1	Goal-setting and action-planning: Objective specification and commitment Self-monitoring: Alcohol-consumption logs Psychoeducation: Alcohol consumption and adverse consequences for obstructive sleep apnoea Cognitive restructuring: Irrational, false or inaccurate beliefs about alcohol consumption Alcohol fading: Reduction of alcohol consumption/number of alcoholic drinks by 30% from baseline Breathing and relaxation techniques: Diaphragmatic breathing and progressive muscle relaxation
Session 2	Review of behavioural goals, action plans, and compliance (participant’s homework) Self-monitoring: Alcohol-consumption logs Cognitive restructuring: Irrational, false or inaccurate beliefs about smoking cessation Alcohol fading: Reduction of alcohol consumption/number of alcoholic drinks by 30% from week 1 Stimulus control: Reduction/abstinence strategies Review of diaphragmatic breathing and progressive muscle relaxation
Session 3	Review of behavioural goals, action plans, and compliance (participant’s homework) Self-monitoring: Alcohol-consumption logs Vicarious and self-reinforcement: Changes in alcohol consumption achieved and benefits Abstinence planning: Setting the day when abstinence starts Stimulus control: Reduction/abstinence strategies Review of diaphragmatic breathing and progressive muscle relaxation
Session 4	Review of behavioural goals, action plans, and compliance (participant’s homework) Self-monitoring: Alcohol-consumption logs Vicarious and self-reinforcement: Changes in alcohol consumption achieved and benefits Problem solving and social skills: High risk situations for drinking alcohol and alternative behaviours Review of all intervention components: Diaphragmatic breathing and progressive muscle relaxation, stimulus control Maintenance and relapse prevention: Difference between lapse and relapse
